Treatment options for UF patients should ideally address 3 goals: (1) relief of signs and symptoms, (2) sustained reduction in fibroid size, and (3) retention or enhancement of fertility if desired. At the same time, treatment should also aim to improve quality of life, minimize side effects, be convenient for patients, and target UF directly [10]. Medical, procedural, or combined treatment options are available for patients with symptomatic UF. However, there were no medications to treat these women in Canada until 2013 when ulipristal acetate (UPA) was approved.

UPA has shown to be more effective than placebo [11] and as effective as the injectable gonadotropin-releasing hormone agonist leuprolide acetate [12] for treating UF symptoms. Leuprolide acetate received Health Canada indication for preoperative improvement of anemia in symptomatic UF women in 2017 [13]. The uptake, long-term clinical and patient-reported outcomes, efficacy, safety, as well as the pharmacoeconomics of indicated and off-label treatment options for these patients in Canada, have yet to be determined.

In the past 15 years, there has been only 1 completed registry for patients with UF who have undergone uterine artery embolization [14]. In the United States, the COMPARE-UF trial is underway [15]. A Canadian prospective patient registry provides the opportunity to address many unanswered questions, particularly the management patterns and outcomes associated with different treatments for UF and patients’ preferences for, and satisfaction with, managing UF symptoms.

With this background in mind, the objectives of this study are to (1) enhance the understanding of the natural history of symptomatic UF, (2) understand Canadian provider and patient preferences for managing symptomatic UF, (3) examine factors that have an impact on the uptake of UF treatment options and compliance with therapy, (4) examine the effectiveness and efficiency of UF treatment options across ethnicities in real-world practice in Canada, and (5) provide real-world data characterizing long-term clinical and patient-reported outcomes, including effectiveness and safety, associated with different UF management options.

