^e^Tool for assessment is the Aberdeen Menorrhagia Severity Scale questionnaire.

^f^EQ-5D-5L: EuroQol 5-dimensions 5-levels survey used to measure health status.

**Table 2 table2:** Schedule of events of the CAPTURE study at procedural intervention and hysterectomy.

Examinations	Procedural intervention^a^			Hysterectomy
	Preoperative	Intraoperative	Postoperative	1-year follow up
Signed informed consent form	—	—	—	—
Inclusion/exclusion criteria	—	—	—	—
Demographics	—	—	—	—
Medical history	—	—	—	—
Fertility wishes	—	—	—	—
Blood work (hemoglobin)^b^	✓	—	—	—
Gynecologic symptoms	—	—	—	✓
Ultrasound of fibroids	✓	—	—	—
Type and location of fibroids	—	—	—	—
Endometrial biopsy	—	—	✓	—
Planned/updated management plan	✓	—	—	—
UFS-QOL^c^	✓	—	✓	✓
Bleeding assessment^d^	✓	—	✓	—
EQ-5D-5L^e^	✓	—	✓	✓
Concomitant medications	✓	—	—	—
Adverse event	✓	✓	✓	—

^a^Procedural intervention is not mandatory in the registry, and data will be collected if physician and patient decide on a procedural intervention to address symptoms associated with uterine fibroids.

^b^To be captured if available.

^c^UFS-QOL: Uterine Fibroid Symptom and Quality of Life questionnaire.

^d^Not required if patient undergoes hysterectomy procedure. Otherwise the tool for assessment is the Aberdeen Menorrhagia Severity Scale questionnaire.

^e^EQ-5D-5L: EuroQol 5-dimensions 5-levels survey used to measure health status.

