### Statistical Analysis

The goal of this study is to establish a registry of Canadian patients with symptomatic UF. We have recruited a sample of 1500 patients to help describe the management of UF in this population.

Initially, exploratory data analysis will summarize all variables of interest by reporting means and standard deviations for continuous variables, and frequencies (percentages) for categorical variables. Analysis of variance will be used to compare continuous variables between treatment groups of interest. Chi-square tests will be used to compare categorical variables between the 2 groups. A linear mixed model will be employed to examine the association between treatment groups while adjusting for other covariates of clinical interest. These variables include demographics, UF history, comorbidities, medications, and medical tests (both current and previous).

The model will include a time-by-treatment-interaction term to determine whether treatments have improved quality of life relative to other treatment groups. Furthermore, a random effect will be included at the patient level to incorporate correlation arising from the repeated measures design of the study.

Since this is an observational registry, missing data and drop-outs (ie, early study termination) are expected. Statistical techniques will be used to examine the missing data (including logistic regression) and, if feasible, multiple imputations will be used to make any adjustments.

Additionally, where imputation techniques are not adequate, sensitivity analysis will be employed. All parameter estimates, confidence intervals, and *P* values will be reported from the model, and a 2-sided significance level of .05 will be used.

The original terms used by participating physicians to identify ADRs will be coded using the Medical Dictionary for Regulatory Activities (MedDRA). The MedDRA system organ class and preferred term will be used to present the number and percentage of patients with ADRs, the drug relationship, seriousness, and intensity of ADRs. Chi-square tests will be employed to compare the number of ADRs between groups of interest.

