### Potential Limitations

This registry has some limitations. The instruments used at different visits are self-reported, which may result in reporting bias. The noninterventional design can lead to selection bias as well as confounding. Finally, failure to follow up and the expected attrition of the participants at subsequent visits following recruitment could impact on the sample size, thus limiting the external validity.

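### The stated covariate adjustment does not reach the time-by-treatment term from which relative improvement in quality of life is to be read

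*Protocol article*

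**What the plan says.** The Statistical Analysis section sets out one comparative model: "A linear mixed model will be employed to examine the association between treatment groups while adjusting for other covariates of clinical interest". The covariates are described by class: "These variables include demographics, UF history, comorbidities, medications, and medical tests (both current and previous"). The term that carries the conclusion is then named: "The model will include a time-by-treatment-interaction term to determine whether treatments have improved quality of life relative to other treatment groups". For the repeated measures, "a random effect will be included at the patient level to incorporate correlation arising from the repeated measures design of the study". Testing is two-sided at .05. The section names no other interaction, and no weighting, matching or conditioning on the baseline score.

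Management is chosen in routine care. The footnote to Table 2 on procedural intervention says that "data will be collected if physician and patient decide on a procedural intervention to address symptoms associated with uterine fibroids". Potential Limitations concedes that "The noninterventional design can lead to selection bias as well as confounding" and offers no remedy. Objectives 4 and 5 in the Introduction concern effectiveness of the different management options.

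**The concern.** Treatment groups in this registry will differ at the start, because symptoms and wishes steer the choice of management. The plan's answer is to put covariates into the mixed model, but its conclusion rests on a difference between groups in change over time. A time-fixed covariate entered as a main effect raises or lowers a patient's scores equally at every visit, so it cannot alter a comparison of changes.

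If a factor such as symptom severity steers treatment choice and also predicts how much a woman's score will move, that imbalance stays in the interaction. The result would be reported as adjusted, while the time-fixed part of the adjustment had done nothing to the term being interpreted. A group could then appear to improve more than another when neither management has an advantage.

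**Working it through.** The article gives no effect size, standard deviation or power calculation, so there is no figure to reproduce. The check is of model structure, followed by a simulation with assumed inputs.

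**Step 1: algebra.** Let A be treatment group, P = 0 at baseline and 1 at follow-up, S a time-fixed confounder and u a patient random intercept. The model with S as a main effect is

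Y = b0 + b1·A + b2·P + b3·A·P + c·S + u + e.

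Subtracting baseline from follow-up within a patient gives

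change = b2 + b3·A + (difference of residuals).

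Both c·S and u have gone. With complete visits, b3 is estimated by the difference in mean change between groups, whether or not S is in the model.

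Now let S also act on change, by g points per SD. The main-effect model then estimates

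b3 + g × (mean S in treated − mean S in comparison).

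If g = 0 the second part vanishes and there is no bias.

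**Step 2: inputs.**
- From the article: 1500 patients, 4 scheduled visits, a patient-level random effect, two-sided .05.
- Assumed: two groups; treatment choice depends on S with log-odds 1 per SD; patient SD 12 and residual SD 14 points; S shifts level by 8 points per SD; g = 0, 1, 2.5 or 5 points per SD; true treatment effect 0. The dropout scenario loses 35% of patients at random.
- Three models were fitted by generalised least squares with known variance components, 500 replicates per scenario: no covariate, S as a main effect, and S plus S-by-time.

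**Step 3: expected bias.** Log-odds of 1 per SD puts the groups 0.826 SD apart on S. Expected bias is 0.826 × g: 0, 0.83, 2.07 and 4.13 points for the four values of g.

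**Step 4: simulated results** (mean interaction estimate, false-positive rate).

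| g (points per SD) | S main effect, complete | S main effect, dropout | S-by-time, complete | S-by-time, dropout |
|---|---|---|---|---|
| 0 | −0.02, 4.8% | 0.01, 6.0% | −0.04, 3.8% | −0.02, 5.2% |
| 1 | 0.81, 15% | 0.84, 18% | −0.04, 3.8% | −0.02, 5.2% |
| 2.5 | 2.05, 69% | 2.08, 64% | −0.04, 3.8% | −0.02, 5.2% |
| 5 | 4.12, 100% | 4.15, 99% | −0.04, 3.8% | −0.02, 5.2% |

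With complete data the main-effect and unadjusted estimates agree to about 3 × 10⁻¹² in every replicate. With dropout they differ by at most 0.32 points in any replicate. The false-positive rates fit the bias-to-SE ratio: at g = 2.5, 2.07 / 0.837 = 2.47, which gives a rejection probability of 69%.

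**Step 5: price of the remedy.** The standard error of the interaction rises from 0.835 to 0.917 with complete data (0.917 / 0.835 = 1.10, about 10% wider intervals) and from about 0.88 to 0.97 with dropout.

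**Step 6: regression to the mean as one possible route.** Assume a 10-point baseline gap and a within-patient correlation of 0.5 to 0.7. If the whole gap came from selection on the measured score, the spurious change would be (1 − 0.7) × 10 = 3 to (1 − 0.5) × 10 = 5 points. If the groups differ in stable severity, each regresses to its own mean and the spurious change is 0. With SD 25, the SE of a difference in change is 25·√(2(1−ρ))·√(2/n): 1.0 to 1.3 for two groups of 750, and 1.4 to 1.8 for four groups of 375.

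**The case against.** The strongest reply is that main-effects-only entry is an inference. The article names one interaction but does not exclude others, and a condensed article may leave covariate form to a full analysis plan. That lowers the severity. It does not remove the point, because the article states both the adjustment and the term that carries the conclusion, and the first as written does not act on the second.

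Three further limits stand. Bias needs a confounder that predicts change, and the documents do not show that one exists or how strong it is. Covariates updated at each visit, such as current medications and tests, can move the interaction. They are measured after treatment starts and may lie on its causal path, so they are not a reliable adjustment for indication. Finally, the stated goal is largely descriptive and confounding is openly acknowledged.

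A reader might be tempted to go further, but the documents do not support these readings:
- *The interaction is certainly biased, or wholly unadjusted.* It is unbiased when g = 0, and visit-updated covariates can alter it.
- *Regression to the mean will produce 3 to 5 points.* That is the upper end of a range starting at 0.
- *Baseline severity and fertility wishes are left out.* The covariate list is not exhaustive, and baseline scores may enter as responses. Whether to condition on baseline or model change is a debatable choice.
- *Categorical outcomes get only an unadjusted test.* The sentence "Chi-square tests will be used to compare categorical variables between the 2 groups" stands in a paragraph that opens with exploratory analysis, and nothing says it is the only analysis.
- *Objective 4, to "examine the effectiveness and efficiency of UF treatment options across ethnicities in real-world practice in Canada", will be answered from a main effect.* The article does not say so. It is silent on the model, and a three-way interaction could meet sparse cells.

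**Conclusion.** The point holds in a conditional form. As written, time-fixed confounders are adjusted in a way that leaves the time-by-treatment term unchanged with complete visits and almost unchanged with dropout. Any pre-treatment factor that influences both management choice and change will bias the comparison of quality of life.

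The size cannot be drawn from the documents. Under the assumptions above it runs from no bias to about 4 points, with a false-positive rate from about 5% to 100%. These figures rest on two groups, one confounder, a separation of about 0.83 SD and dropout at random. The structural result (Step 1) rests on none of the assumed values. Severity: should-fix.

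**What to change.** For the comparative quality-of-life analysis, state one of the following:

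1. Covariate-by-time terms in the mixed model for a limited, named set of pre-treatment confounders, including symptom severity, fertility wishes, and fibroid type and size, all of which Table 1 schedules at baseline.
2. Propensity-score weighting for management choice, estimated from pre-treatment data only.

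In either case, say that medications and tests recorded after treatment starts will not be relied on to adjust for confounding.

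Make the main comparison among women initiating treatment and women under watchful waiting. The Participants section also admits women already on treatment, and their enrolment values may not be pre-treatment.

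The cost is wording and programming, with no new data collection. Intervals widen somewhat (about 10% in the simulation with one confounder, more with several), and the comparative set is smaller than 1500. The article expected the last visit in February 2020, after its publication in November 2018, so the change could have been fixed before follow-up was complete.

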### Hysterectomy Postoperative Follow Up

If a patient undergoes a hysterectomy, a follow-up visit will occur 1 year after the hysterectomy (in addition to the postoperative visit). This follow up will replace all remaining scheduled follow-up study visits. Information on postoperative symptoms, overall satisfaction, UFS-QOL-Hysterectomy, and EQ-5D-5L will be obtained. Once this follow up is completed, the patient will be deemed to have completed all study visits.

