### Statistical Methods

The analysis will include all patients enrolled in the study who have been entered into the database.

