## Results

Participant recruitment for this registry began in July 2015. The registry has recruited 1500 patients, with the first patient enrolled in the second half of 2015. Patient follow up will occur for up to 2 years, with the last patient visit occurring in 2020. It is anticipated that national/industrial funding will be available to continue this initiative beyond 2020 based on the information generated from this registry.

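### The chi-square test on the number of ADRs leaves the counting unit unclear and takes no account of time at risk

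*Protocol article*

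**What the plan says.** All of the following is in the protocol article.

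- **The test (Statistical Analysis).** "Chi-square tests will be employed to compare the number of ADRs between groups of interest".
- **The summary just before it (Statistical Analysis).** "The MedDRA system organ class and preferred term will be used to present the number and percentage of patients with ADRs". Here the unit is the patient.
- **Correlation within patients (Statistical Analysis).** "a random effect will be included at the patient level to incorporate correlation arising from the repeated measures design of the study". This belongs to the linear mixed model; nothing similar is attached to the ADR test.
- **Significance level (Statistical Analysis).** "a 2-sided significance level of .05 will be used". This stands in the sentence on results reported from the model. No separate level is given for ADRs.
- **Analysis set (Statistical Methods).** "The analysis will include all patients enrolled in the study who have been entered into the database".
- **Follow-up (Results).** "Patient follow up will occur for up to 2 years".
- **After hysterectomy (Hysterectomy Postoperative Follow Up).** A visit one year after surgery is added, and "This follow up will replace all remaining scheduled follow-up study visits".

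**The concern.** The article names both the test and the quantity tested, so this is a stated rule and not a detail left to an unseen analysis plan. Two things can go wrong if it is followed as written.

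**Clustering.** One patient can contribute several ADRs, because they are assessed at each scheduled follow-up visit, before an operation and at unscheduled visits. A chi-square on event totals takes each reaction as an independent unit, so its variance is too small when reactions cluster within patients.

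**Time at risk.** A chi-square on counts or on proportions has no time denominator. Patients observed or treated for longer have more opportunity to record a reaction.

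Safety across management options is part of the fifth objective in the Introduction, and this is the only between-group test that the article names specifically for ADRs.

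**Working it through.** The article gives no ADR rate, dispersion, group size or power figure for this comparison, so it has no figure of its own to reproduce. Every numerical input below is an assumption unless marked otherwise.

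**1. Unit.** Side by side, the summary sentence counts patients with ADRs and the test sentence compares the number of ADRs. Steps 2 and 3 take the test literally, as total ADRs per group set against totals expected from the patient numbers.

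**2. Effect of clustering, equal exposure.** Let φ be the variance-to-mean ratio of ADRs per patient. With no true difference, the two-sided size of the event-level test is

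2 × (1 − Φ(1.96 / √φ)).

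For negative binomial counts with mean μ and shape k, φ = 1 + μ/k.

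| μ | k | φ | 1.96/√φ | Size, formula | Size, simulated |
|---|---|---|---|---|---|
| 0.3 | 1 | 1.3 | 1.72 | 8.6% | 9.2% |
| 0.6 | 1 | 1.6 | 1.55 | 12.1% | 11.9% |
| 0.6 | 0.5 | 2.2 | 1.32 | 18.6% | 18.8% |

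The simulations used 300 patients per group and 3000 replicates. A chi-square on patients with at least one ADR stayed at 4.5% to 5.2%. With φ = 1 the formula gives exactly 5%, so the inflation exists only if ADRs cluster.

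**3. Effect of unequal time at risk, equal true rates.** Take 200 patients per group and 0.5 ADRs per patient per 24 months. One group is observed for 24 months and the other for 12. Expected events are 200 × 0.5 = 100 and 200 × 0.25 = 50. Set against 75 and 75, the chi-square is 2 × 25²/75 = 16.7, far above 3.84, although the rates are the same.

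The proportion of patients with an ADR behaves in the same way. With Poisson counts it is 1 − exp(−mean):

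- 0.5 per 24 months: 1 − e^(−0.5) = 39.3% over 24 months, 1 − e^(−0.25) = 22.1% over 12 months.
- 0.2 per 24 months: 18.1% and 9.5%.

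The next table gives simulated rejection rates with no true rate difference (3000 runs per setting; means 0.2 and 0.5; φ of 1 and 2; groups of 200/200 and, for mean 0.5, also 750/750).

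| Exposure ratio | Chi-square on ADR totals | Chi-square on patients with an ADR | Person-time rate, patient-level robust variance |
|---|---|---|---|
| 0.75 | 21% to 95% | 12% to 90% | 5% to 6% |
| 0.5 | 68% to 100% | 38% to 100% | 5% to 6% |

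Moving to patients as the unit therefore cures clustering but not unequal exposure. The person-time comparison handles both.

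**4. Does the article give reason to expect unequal time at risk?** Yes, in five places.

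- Participants: women already on treatment are enrolled alongside those starting it and those under observation.
- Withdrawal of Participants: data collection stops at withdrawal.
- Visits at Three to Six Months, Twelve Months, and Twenty-Four Months: ADRs are assessed when a drug was prescribed at the visit before, so the opportunity to record one depends on treatment.
- Hysterectomy Postoperative Follow Up and Table 2: the remaining schedule is replaced, and adverse events are not ticked at the one-year hysterectomy visit.
- Results: two years is an upper limit on follow-up. Statistical Analysis adds that drop-out is expected.

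**The case against.** The strongest reply is that the authors meant patients with ADRs. The preceding sentence counts patients, and earlier in the same section chi-square tests are assigned to categorical variables. An ADR total is not one, but whether a patient had an ADR is. On that reading the clustering problem and the 9% to 19% figures fall away. This is a fair reading and may be the intended one. The sentence still needs correcting, and the time-at-risk problem remains.

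A second reply is that the study is descriptive: "We have recruited a sample of 1500 patients to help describe the management of UF in this population". The groups are not randomised, Potential Limitations already admits selection bias and confounding, and the .05 level is stated for model results. That stands in part. An exact type I error for a crude ADR comparison does not decide whether the registry is sound, which lowers the severity.

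A third reply is that exposure windows and rate models belong in the analysis plan. Their details do. But the article itself fixes a test that has no place for time.

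A reader might go further and infer that the planned test will produce false-positive safety differences that cannot be interpreted at all. The documents do not support that. Inflation needs clustering or unequal exposure, neither of which is quantified, and shorter exposure in one group can equally hide a real excess. The exact statement is that a crude difference is not interpretable as a difference in risk without time at risk. Nor does hysterectomy remove a patient from the registry at surgery, since postoperative and one-year visits follow.

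**Conclusion.** The point holds, with moderate severity. As written, the ADR comparison counts reactions where the adjoining summary counts patients. On the literal reading its size rises from 5% to about 9% to 19% for assumed variance-to-mean ratios of 1.3 to 2.2. That part depends on the literal reading and on assumed dispersion.

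The time-at-risk part holds under either reading, because the article's own design makes exposure and follow-up unequal. Its size cannot be fixed from the article. In the settings tried, an exposure ratio of 0.75 or 0.5 with equal true rates raised rejection to between 12% and 100%, depending on the test, ADR rate, dispersion and group size. The direction can go either way.

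**What to change.** Replace the test sentence with a rule along these lines:

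> The number and percentage of patients with at least one ADR will be shown by group and compared by chi-square or, where counts are sparse, Fisher's exact test; this comparison is crude. The between-group comparison of ADRs will be based on rates per person-time, from a negative binomial or robust Poisson model with log time at risk as offset, patient-level variance and the covariates listed for the linear mixed model. Rate ratios with 95% confidence intervals will be reported.

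The person-time model is the essential part, because the patient-level chi-square alone does not deal with unequal exposure. The covariates are needed because the groups are not randomised.

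Time at risk should be time on treatment if drug start and stop dates are recorded. Table 1 lists concomitant medications, but the article does not say that their dates are captured, so this must be confirmed. Otherwise, use time under observation from visit dates.

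The cost is a change of wording and slightly more analysis work, with no change to the visit schedule. If drug dates are incomplete, exposure time will be approximate, and the report should say so.
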